## Assessment of SAEs

Classification and causality of Adverse Events (AEs) will be conducted by sub-investigators and reviewed by the CI. The CI cannot downgrade the initial classification and if there is disagreement which cannot be resolved during formal discussion then the assessment of the sub-investigators will be accepted. The CI, can however, upgrade the seriousness of an event without consultation with the sub-investigator.

Only SAEs felt to be related to study procedures will be reported as described in section 12.5.

## Expected AEs

No intervention or treatment is being provided. We also do not anticipate any study procedure related AE or SAE’s, but if these do occur, they will be recorded in the hospital notes and case report form (CRF).

In adult patients' temporary health deterioration and possible admission to hospital is expected and will be recorded as part of the study.

In the ‘Mini’ and ‘Midi’ study AEs related to CFTR modulators such as liver dysfunction or cataracts will be reported through the yellow card scheme, and participants will be medically managed by the paediatricians in the team. This may lead to extra clinical visits and further testing where clinically required.

## Reporting of SAEs to the sponsor and the REC

The CI and their research team at RBHH are responsible for reporting study procedure related SAEs to the Research Office immediately and/or within 24 hours of becoming aware of the event in accordance with the process outlined below.

A study procedure related SAE occurring to a research participant will be reported to the Research Ethics Committee (REC) that gave a favorable opinion of the study, the study Sponsor (RBHH Research Office) and the local R&D Office where in the opinion of the CI/PI the event was:

- **‘Related’**: that is, it resulted from administration of any of the study procedures; and
- **‘Unexpected’**: that is, the type of event is not listed in the protocol as an expected occurrence.

Reports of related and unexpected SAEs will be submitted to the REC within 15 days of the CI/PI becoming aware of the event; using the SAE reporting form for non-CTIMPs published [on the HRA website and entitled non-CTIMP safety report to REC](file:///C:\Users\[name]\AppData\Local\Microsoft\Windows\INetCache\06_Drafts\03_RO%20Guidance%20Documents\on%20the%20HRA%20website%20and%20entitled%20non-CTIMP%20safety%20report%20to%20REC). The form should be completed in typescript and signed by the Chief Investigator (CI) prior to submission to the REC.

All SAEs that are to be reported to the REC should also be forwarded to the Research Office in parallel and must be recorded, signed and dated by the Investigator at site. Research Office accepts study specific SAE forms, HRA SAE Form or RBHH template SAE Reporting Form available [here](http://www.rbht.nhs.uk/research/for-researchers/setting-up-and-managing-a-project/policies/templates/).

Information can be submitted to the Research Office in electronic format:

- E-mail: [[contact]](mailto:[contact]).

Following submission by the CI, the coordinator of the main REC will acknowledge receipt of safety reports within 30 days. It is the responsibility of the CI and his/her research team to send a copy of the SAE notification and acknowledgement receipt to the Research Office.

The study team also has the responsibility to report SAEs occurring in a certain period (28 days) after a patient completes the study. Any SAEs reported to the Investigators during this phase must be documented in the patient’s medical notes and submitted *via* an SAE reporting form.

## The type and duration of Follow up

This study does not include any intervention. Therefore, no follow up requirement for AE/SAEs related to the study are anticipated for the participants. However, the study team includes paediatric and adult trained doctors who will be able to support participants to ensure appropriate management and follow up is in place in the RBH or elsewhere if needed for any other medical issues that arise. This may include the need for extra clinic appointments, investigations and treatments. These will be documented in the final analysis.

## Annual Progress Reports (APRs)

The Chief Investigator will prepare the APR for the study. It will be sent to the REC by the CI within 30 days of the anniversary date on which the favourable opinion was given by the REC, and annually until the study is declared ended.

## Reporting Urgent Safety Measures

The Sponsor and/or the Investigator may take appropriate urgent safety measures in order to protect the subjects of a clinical study against any immediate hazard to their health or safety. If safety measures are taken, REC approval is not required before the measure is taken.

The Investigator will immediately and in any event no later than 3 days from the date the measures are taken, give written notice to the REC and the study Sponsor of the measures taken and the circumstances giving rise to those measures.

In order to prevent any delays in the reporting timelines the Sponsor has delegated this responsibility to the CI/PI. Therefore, the CI/PI must report any urgent safety measures to the REC directly, and in parallel to the Sponsor. The REC coordinator will acknowledge receipt of urgent safety measures within 30 days.

## Notification of Serious Breaches of GCP and/or the protocol

To ensure compliance with the REC favourable ethical opinion, the sponsor should report to the REC any serious breaches of the protocol or of the principles of Good Clinical Practice. A “serious breach” is defined as a breach of the protocol or, of the principles of Good Clinical Practice which is likely to affect to a significant degree the safety or physical or mental integrity of the study participants, or the scientific value of the research. There is no requirement to notify minor breaches of GCP or the protocol.

It is the responsibility of the CI to ensure that any non-compliance is reported to the Research Office, to allow appropriate investigation.

Reports of non-compliance should give details of the issues that have occurred, the location, who was involved, the outcome and any information given to participants. In the instance of reporting non-compliance as a serious breach, the Research Office will work with the study team to generate an explanation to ensure the REC is informed of further action the sponsor plans to take.

# Data management and quality assurance

## Confidentiality

All data will be handled in accordance with the Data Protection Act 1998, NHS Caldecott Principles, The Research Governance Framework for Health and Social Care, 2nd Edition (2005), and the condition of the main REC approval.

The Case Report Forms (CRFs) will not bear the subject’s name or other personal identifiable data. A study Identification Number (ID) will be used for identification. This number will not include any personal information. Only the unique ID will be used on any study-related information collected. Information that contains a participant's identity will remain only with the study team.

No information or records that disclose a participant's identity will be released without consent unless required by law.

## Data collection tool

To support continuity of care data collected will be recorded on the subject's secure password protected Royal Brompton Hospital electronic medical notes. Case Report Forms (CRF) have been designed to record specific information required from the medical notes for study data analysis. These CRFs have been designed by the CI and Sub-I's and the final version will be approved by the Sponsor. CRF’s will be electronic and held on REDCap, a secure password protected database.

It is the Investigator’s responsibility to ensure the accuracy of all data entered and recorded in the CRFs. The Delegation of Responsibilities Log will identify all trial personnel responsible for data collection, entry, handling and managing the database.

## Data handling and analysis

REDCap is a secure password protected web-based database which will be used for data entry, storage and analysis. Disaster recovery of this data is included on these servers, with files regularly backed up.

The CRF saved on REDCap will be designed to ensure all the required data is collected. The sub-investigators and other delegated staff will be responsible for data entry. Staff will be trained to ensure consistency in data input and adherence to the protocol.

All samples transferred to other sites will only be coded with data ID rather than patient identifiable data. Results of this will be processed in batches and the results returned to researchers via a secure transfer.

Data analysis will be done when final study data is available as no formal interim analysis is planned, and prior to this a statistical analysis plan will be written, taking into account the numbers recruited.

# Archiving arrangements

The study documents (including the Trial Master File (TMF), Case Report Forms (CRFs), Informed Consent Forms along with the trial database) will be kept for a minimum of five years. They will be stored in locked offices within the Royal Brompton and Harefield NHS Foundation Trust site for the duration of the study. The Chief Investigator is responsible for the secure archiving of study documents. The study database will also be kept electronically on the Trust computer network, for a minimum of five years.

The approved repository for longer retention of local materials for studies that involve RBHH patients is OASIS Group UK. The study documentation will be prepared for archiving by the study team in line with the Research Office Archiving SOP and the transfer will be arranged by the Research Office.

# Statistical design

## Statistical input in study design

All three sub-studies described in this protocol are observational in design. Descriptive analyses will be used to report the data. Within this context no complex statistical analyses are anticipated which require statistician input in the design phase and a statistical analysis plan will be written prior to final analysis.

## Endpoints

### Primary endpoints

As an observational study, a combination of multiple endpoints will be monitored to identify areas of interest that may warrant and benefit from future investigation in larger studies.

Below are the endpoints which will be explored based on the currently available literature and research in the field.

*‘Mama’ sub-study*

1. Change in percent predicted FEV_1_ (ppFEV_1_) from pre-conception/baseline to end of pregnancy, and at 12- and 24-months post-partum.
2. Incidence of CF-related pulmonary complications during pregnancy.
3. Incidence of premature delivery (defined as birth <37 weeks gestation).

*Combined ‘Mini’ and ‘Midi’ sub-study*

1. The number of participants with:
2. Liver dysfunction (ALT/AST/GGT/bilirubin above upper limit of normal). This is prospectively obtained in the ‘Mini’ sub-study, and retrospectively reviewed from medical records in the ‘Midi’ sub-study.
3. Presence of congenital abnormalities including cataracts (based on medical history and examination)
4. The number of participants with normal IRT subsequently diagnosed with CF (based on a combination of CF genetic tests, sweat chloride, and faecal elastase where appropriate)
5. The number of participants with an abnormal lung clearance index (LCI) (‘Midi’ only)

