# Study Aims and Objectives

## Primary aims

1. **Sub-study ‘Mama’**: To describe the impact of pregnancy and the first 12-24 months of parenthood in females with cystic fibrosis on their physical and psychological health.
2. **Sub-study ‘Mini’ & ‘Midi’:** To collect clinical data that will enable assessment of health outcomes in offspring of parents with CF in the short (up to 24 months) and medium-term (aged three-to-six years)

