### Medical History

For adult participants who are patients under the Royal Brompton CF service, permission to access past medical details from medical records (including from the UK CF Registry if participant has previously consented to this) will be requested to be used in analysis of the study results.

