### Exploratory endpoints

*‘Mama’ sub-study*

Quantitative endpoints are:

1. Obstetric-specific:
   1. Caesarean section rate
   2. Incidence of medically initiated delivery for pulmonary indication
   3. Incidence of intrahepatic cholestasis
   4. Incidence of pregnancy induced hypertension.
   5. Incidence of pre-eclampsia
   6. Incidence of gestational diabetes
   7. Incidence of large or small for gestational age infants
   8. Incidence of postnatal anxiety/depression (as noted by EPNDS or patient-reported following clinical assessment by other healthcare providers)
   9. Obstetric outcomes according to chronic airways pathogen colonisation history
   10. Obstetric outcomes according to micro-nutritional or early pregnancy hormonal status.
   11. Obstetric outcomes according to diabetes status and therapy (CF diabetes, gestation diabetes, no diabetes)
2. CF-specific:
   1. Incidence of pulmonary exacerbations during pregnancy and within first 24 months requiring oral and/or IV antibiotics.
   2. Variability in lung function during and post-pregnancy as shown by OE-MRI
   3. Sweat chloride levels during pregnancy, and variability per trimester.
   4. Change in weight from pre-conception until pre-delivery.
   5. Change in CFQ-R, EQ-5D-5L, PHQ9 and GAD7 scores.
   6. Bronchial artery size assessment (by MRI) at baseline/pre-conception, antenatal and post-partum (6-12 months).
   7. Change in haemoptysis frequency from baseline, and during pregnancy (as per number episodes per person-years pregnant), and post-partum.
   8. Change in weight according to breast-feeding status in first 24 months post-partum.
   9. Validation of CFTRm assays in serum and breastmilk.

Qualitative endpoints:

1. Thematic analysis of experiences of females with CF throughout:
   1. Family planning,
   2. Pregnancy and childbirth,
   3. Early parenthood.

*Combined ‘Mini’ and ‘Midi’ sub-study*

Exploratory endpoints are:

1. Number of participants with below neonatal birth outcomes:
   1. Prematurity (defined as being born < 37 weeks' gestation)
   2. Low birth weight < 2^nd^ centile
   3. Special care or neonatal intensive care unit admission
2. Frequency of raised blood pressure (>95^th^ centile for age, sex and height on two separate readings)
3. Frequency of faltering growth (definition as per NICE guidelines [NG75])
4. Frequency of delayed development past limit ages in gross motor, vision and fine motor, hearing, speech and language, and social domains. (see appendix 2)

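### Two 'Mama' event endpoints, pulmonary complications and exacerbations, have no pre-conception window and no stated person-time, so neither can be set against the woman's own earlier rate

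*Protocol*

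**What the plan says.** Protocol section 5.1 gives the 'Mama' aim as "To describe the impact of pregnancy and the first 12-24 months of parenthood in females with cystic fibrosis on their physical and psychological health". Section 7.1 admits only women who are pregnant or planning a pregnancy, and the only group comparison named in section 15.4.2 is between those exposed and not exposed to CFTR modulators.

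Four lung-related endpoints matter here:
- Primary endpoint 1 (15.2.1): change in ppFEV1 "from pre-conception/baseline to end of pregnancy, and at 12- and 24-months post-partum".
- Primary endpoint 2 (15.2.1): "Incidence of CF-related pulmonary complications during pregnancy".
- Exploratory (15.2.2): "Incidence of pulmonary exacerbations during pregnancy and within first 24 months requiring oral and/or IV antibiotics".
- Exploratory (15.2.2): "Change in haemoptysis frequency from baseline, and during pregnancy (as per number episodes per person-years pregnant), and post-partum".

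The protocol also arranges access to history. Section 9.3.3 seeks "permission to access past medical details from medical records (including from the UK CF Registry if participant has previously consented to this", section 9.3.2 includes a review of earlier history and registry data at baseline, and section 15.3.2 adds consent for retrospective access to clinical data for women who enrol part-way through pregnancy.

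**The concern.** Describing an impact implies a before and an after. With no non-pregnant group, the before can only come from the same woman. Primary endpoint 2 and the exacerbation endpoint both start counting at pregnancy, so neither contains it. The exacerbation endpoint also spans two periods of very different length, about 9 and 24 months, with no denominator stated.

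This matters for how the results are used. Section 4.2.2 cites work reporting more exacerbations in the first year of parenthood, which is a comparative statement. Section 4.3.3 expects the findings to improve pre-conception counselling, and section 15.3.1 expects them to help power later studies. A bare incidence serves neither purpose well, because a reader cannot tell how much of it would have occurred anyway.

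**Working it through.** **The endpoints side by side**

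| Endpoint | Pre-pregnancy reference | Person-time stated |
| --- | --- | --- |
| ppFEV1 change (primary 1) | Yes, a level | Not applicable |
| Pulmonary complications (primary 2) | No | No |
| Exacerbations (exploratory) | No | No |
| Haemoptysis (exploratory) | Yes, baseline | Yes, for pregnancy |

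The gap is confined to the two middle rows.

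**Inputs.** From the protocol: 20-25 women (15.3.2) and post-partum follow-up of 24 months (6.1). Pregnancy is taken as 9 months, or 0.75 years. The protocol gives no event rate, so steady rates of 0.3, 0.5 and 1.0 per woman-year are assumptions chosen to show a range. It also states no power or precision figure for these endpoints, so there is none to reproduce.

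**Step 1. Women with at least one event in pregnancy, if pregnancy has no effect.** P = 1 − exp(−rate × 0.75):
- 0.3 per year: 1 − exp(−0.225) = 20%
- 0.5 per year: 1 − exp(−0.375) = 31%
- 1.0 per year: 1 − exp(−0.75) = 53%

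An observed incidence anywhere in this range is compatible with no change, and only the woman's earlier rate can narrow it.

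**Step 2. Unequal periods.** At any constant rate, the ratio of raw counts is 24/9 = 2.67. A total over the post-partum period would be about 2.7 times the pregnancy total with no true change.

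**Step 3. What a pre-conception year would provide.** Expected events in the 12 months before conception run from 20 × 0.3 = 6 to 25 × 1.0 = 25. In pregnancy they run from 20 × 0.3 × 0.75 = 4.5 to 25 × 1.0 × 0.75 = 18.75. With Poisson counts and a true rate ratio of 1, the 95% limits are 1 divided and multiplied by exp(1.96 × √(1/E₁ + 1/E₀)), where E₁ and E₀ are the expected events in pregnancy and before conception:
- 20 women, 0.3 per year: exp(1.96 × √(1/4.5 + 1/6)) = 3.4-fold either way
- 25 women, 1.0 per year: exp(1.96 × √(1/18.75 + 1/25)) = 1.8-fold either way

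That is imprecise, but it is a contrast, which the two endpoints do not now offer.

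**Step 4. ppFEV1.** The endpoint already has a starting level. Two smaller matters remain. Section 15.3.2 allows enrolment at any stage of pregnancy, so the baseline may be a pregnancy value unless earlier records are used. Change to 24 months post-partum also spans about 0.75 + 2 = 2.75 years from conception, so it includes whatever background CF decline occurs. The documents give no rate of decline, and no figure for it is relied on here.

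**The case against.** **It is a descriptive study.** The objectives are to record, section 15.4.2 is descriptive, and section 15.2.1 says the endpoints are meant to identify areas for larger studies. A reader might infer that ordinary CF events and decline will be presented as effects of pregnancy, or that the primary aim cannot be answered. The documents do not support either: no causal test or attribution is specified, and an incidence in pregnancy is a legitimate description. What remains is that a descriptive study can also describe the prior rate, and the word impact invites the comparison.

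**The reference is not missing throughout.** A reader might infer that all the 'Mama' lung endpoints lack a pre-pregnancy reference. ppFEV1 and haemoptysis do not. Requiring individual prior ppFEV1 slopes would be a debatable trade-off: extrapolating them is unstable, and a modulator start can break the trend.

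**Stretched evidence.** Adding a 12-month pre-conception lead to 33 months gives 45 months, which exceeds the three-year study unless the baseline comes from records. Section 12.4 says that in adult patients "temporary health deterioration and possible admission to hospital is expected and will be recorded as part of the study"; this concerns events during the study and gives no rate outside pregnancy. Nor does the protocol say that raw counts over 9 and 24 months will be compared; incidence could be read as a rate.

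**It could wait for the SAP.** Denominators and rate ratios often do. The pre-conception window is different: section 13.2 says the CRF takes from the notes the specific items needed for analysis, while sections 13.3 and 15.1 place the SAP before final analysis. If no endpoint calls for the prior year, nothing ensures that it is abstracted.

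**A prior year is an imperfect control.** Women may conceive when they are well, so that year may be unusually good and a later rise may be partly regression to the mean. This stands and should be reported.

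**Conclusion.** The point holds for primary endpoint 2 and the exploratory exacerbation endpoint. Both are bare incidences that start at pregnancy, while haemoptysis in the same protocol has a baseline and person-years. With no effect of pregnancy, 20% to 53% of women would still have an event during it, and raw counts would differ 2.7-fold between the two periods. The percentages rest on assumed steady rates of 0.3 to 1.0 per year and a 9-month pregnancy; the 2.7 rests only on a constant rate and the two durations. For ppFEV1 the point reduces to a baseline rule and a caveat. This is a worthwhile, inexpensive improvement to a descriptive study, and it does not invalidate the aim.

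**What to change.** In sections 15.2.1 and 15.2.2, define pulmonary complications and exacerbations as rates per person-year over four periods: the 12 months before conception, pregnancy, 0-12 months post-partum and 12-24 months post-partum. Take the first period from medical records and the Registry, and add a matching CRF field now. Report descriptive within-woman rate ratios, with confidence intervals, against the pre-conception year.

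For ppFEV1, take the baseline from pre-conception records for women enrolled during pregnancy, and state that change to 12 and 24 months includes background CF decline. Showing earlier ppFEV1 values is optional and descriptive.

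The cost is modest record abstraction for about 20-25 women, with no new visits or tests. The ratios will be imprecise: at a true ratio of 1, limits of about 1.8-fold to 3.4-fold either way under the assumed rates. The report should note that the pre-conception year may be unusually good because of the timing of conception, or altered by a recent modulator start.

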## ‘Mini’ and ‘Midi’ sub-study assessments

### Summary flow chart of study assessments (Table 2 & 3)

‘Mini’ Sub-Study (Table 2)

A phone or video call will take place before the first in-person visit to review inclusion/exclusion criteria and will be repeated in person at the first visit.

There are no strict time-windows in which each visit must be completed, but preferably they should be as close as possible to the designated visit. If a participant is enrolled at an older age than 8 weeks (for example any age up to 12 months), all the procedures from Visit 1 should still take place at the first visit, with the schedule then proceeding as below.

| Study Procedure | Visit 1  4-8 weeks age | Visit 2  6 months of age | Visit 3  12 months of age | Visit 4  24 months of age |
| --- | --- | --- | --- | --- |
| **For all children enrolled** | | | | |
| Informed consent | X |  |  |  |
| Inclusion/exclusion criteria | X |  |  |  |
| Demographics | X |  |  |  |
| Baseline assessments^1^ | X |  |  |  |
| Medical History^2^ | X | X | X | X |
| Physical examination^3^ | X | X | X | X |
| Liver function blood tests^4^ | X | X | X^5^ | X^5^ |
| Sweat test^6^ | X | X^7^ |  |  |
| Faecal elastase^8^ | X | X^7^ |  |  |
| Cranial ultrasound^9^ | X |  |  |  |
| **Only for children exposed to CFTRm** | | | | |
| Document ophthalmological review^10^ | X |  | X^5^ | X^5^ |
| CFTRm assay^11^ | X | X | X^5^ | X^5^ |
| **Key**:  X: Planned completion date  Highlighted in grey: tests that are additional to standards of practice. Note that all tests for children not exposed to CFTRm are additional to standards of practice.  1. See section 9.4.2  2. See section 9.4.4.  3. See section 9.4.5.  4. See section 9.4.6  5. Only if breastfed and exposed to CFTR modulator in last 6 months  6. See section 9.4.8  7. If exposed to CFTRm via breast feeding at the 4 – 8 weeks visit to repeat at 6 months. If still exposed at 6 months repeat at 12 months and so on, as exposure to CFTRm via lactation could affect results  8. See section 9.4.9.  9. See section 9.4.10  10. See section 9.4.3  11. See section 9.4.7 | | | | |

‘Midi’ Sub-study (Table 3)

As for ‘Mini’, a phone or video call will take place before the first in-person visit to review inclusion/exclusion criteria and will be repeated in person at the first visit.

All tests for all participants in the ‘Midi’ study are additional to standards of practice.

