| Study Procedure | Age 3 - <5 years at time of recruitment | | Age 5+ at time of recruitment |
| --- | --- | --- | --- |
|  | First visit | Second visit (once aged 5+) | Single visit |
| Informed consent | X |  | X |
| Inclusion/exclusion criteria | X |  | X |
| Demographics | X |  | X |
| Baseline assessments^1^ | X |  | X |
| Medical history^2^ | X | X | X |
| Physical examination^3^ | X | X | X |
| Sweat test^4^ | X |  | X |
| O2 enhanced Lung MRI^5^ |  | X | X |
| Lung clearance index^6^ | X | X | X |
| **Key**:  X: Planned completion date  1. See section 9.4.2  2. See section 9.4.4.  3. See section 9.4.5.  4. See section 9.4.8  5. See section 9.4.12  6. See section 9.4.11 | | | |

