### Liver function blood tests

A heel/toe prick device will be used to obtain around 1ml of capillary blood into an SST bottle and sent to the local laboratory for analysis for liver function tests (ALT, ALP, AST, Gamma-GT, total bilirubin, conjugated bilirubin, unconjugated bilirubin, and albumin). In circumstances where parents prefer venepuncture over a heel prick this will be an option. Tests will be analysed as per local lab procedures.

Three monthly liver function tests are our local standard of practice for infants with continued exposure to CFTRm in the first year. The blood test temporally closest to the study visit will be recorded. If any abnormalities are found, there may be a requirement for more regular testing. This will also be recorded.

For infants not exposed to CFTRm this test is for research purposes only, and as with all other tests optional.

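### The primary liver endpoint has no set visit or denominator, while infants with continuing exposure through breast milk are scheduled for up to four liver tests against two for non-exposed infants, so an ever-abnormal comparison in 'Mini' is tilted towards exposure

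*Protocol*

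**What the plan says.** **Endpoint.** Section 15.2.1 lists, for 'Mini' and 'Midi' combined, the number of children with "Liver dysfunction (ALT/AST/GGT/bilirubin above upper limit of normal". It gives no visit, age window, confirmation rule or denominator. The exploratory blood pressure endpoint in section 15.2.2 does carry a repeat rule: "Frequency of raised blood pressure (>95^th^ centile for age, sex and height on two separate readings".

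**Sources.** The liver endpoint draws on two kinds of data: "This is prospectively obtained in the ‘Mini’ sub-study, and retrospectively reviewed from medical records in the ‘Midi’ sub-study". Table 3 schedules no liver test in 'Midi'.

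**Schedule.** The row for all enrolled 'Mini' children in Table 2 (section 9.4.1) reads "Liver function blood tests^4^ | X | X | X^5^ | X^5". Footnote 5 limits visits 3 and 4: "Only if breastfed and exposed to CFTR modulator in last 6 months". The key to Table 2 adds that every test in a non-exposed child is beyond standard practice.

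**Clinical testing.** Section 9.4.6 states: "Three monthly liver function tests are our local standard of practice for infants with continued exposure to CFTRm in the first year". Only the result nearest each study visit is recorded. On follow-up of abnormal values it says: "If any abnormalities are found, there may be a requirement for more regular testing. This will also be recorded". For non-exposed infants the test is optional and for research only.

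**Analysis.** Section 15.4.2 names a chi-square or Fisher's exact test for categorical comparisons of exposed with non-exposed children. The confounders it names do not include number of tests or data source. Its one sensitivity analysis concerns age at enrolment.

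**The concern.** With no visit or confirmation rule, the plain reading of the endpoint is that a child counts once any of the four analytes has exceeded the limit on any recorded test. Such a count rises with the number of tests. Here the schedule makes that number depend on the exposure being compared: an infant with continuing exposure through breast milk can have four scheduled tests, a non-exposed infant at most two. Some of any excess in the exposed group would then reflect opportunity to be tested.

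'Midi' adds a second problem. Its liver results exist only where someone ordered a test in routine care, and non-exposed children have no routine liver tests.

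The study is meant to flag topics for larger studies and to help power them, and section 4.2.2 already raises hepatotoxicity as a suspicion. An artefact in the suspected direction could easily be taken for a signal.

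**Working it through.** The protocol gives no event rate, power or alpha for this endpoint, so there is no stated figure to reproduce. The check asks what the comparison would show if exposure had no effect.

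**Inputs from the protocol**
- Scheduled tests in 'Mini': 2 for non-exposed infants and for those exposed only in utero; up to 4 with continuing exposure through breast milk (Table 2, footnote 5).
- Expected numbers: 25 to 35 in 'Mini' (30 used) and about 20 in 'Midi' (section 15.3.2).

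**Assumptions, not in the protocol**
- Chance p that a panel shows at least one value above the limit: 0.025 to 0.15. The value 0.096 corresponds to four independent analytes, each with a 2.5% upper tail: 1 − 0.975⁴ = 0.096.
- Share s of exposed infants who have both the visit 3 and the visit 4 test: 0 to 1.

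**Step 1: 'Mini', independent results.** P(ever abnormal in k tests) = 1 − (1 − p)^k.

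| p | 4 tests | 2 tests | Ratio |
|---|---|---|---|
| 0.025 | 9.6% | 4.9% | 1.95 |
| 0.05 | 18.5% | 9.8% | 1.90 |
| 0.096 | 33.2% | 18.3% | 1.82 |
| 0.15 | 47.8% | 27.8% | 1.72 |

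**Step 2: only some exposed infants have the later tests.** The ratio is [s(1 − (1 − p)⁴) + (1 − s)(1 − (1 − p)²)] / (1 − (1 − p)²), which simplifies to 1 + s(1 − p)².
- s = 0: 1.0.
- s = 0.25: 1.23 (p = 0.05) and 1.20 (p = 0.096).
- s = 0.5: 1.45 and 1.41.
- s = 1: 1.90 and 1.82, as in step 1.

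**Step 3: results correlated within a child.** Under a beta-binomial model with correlation ρ and s = 1:
- ρ = 0.2: 14.4% v 8.8% (1.63) at p = 0.05; 26.2% v 16.5% (1.58) at p = 0.096.
- ρ = 0.5: 10.1% v 7.4% (1.36) at p = 0.05; 18.7% v 13.9% (1.34) at p = 0.096.

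**Step 4: pooling with 'Midi', one possible denominator.** Take 30 'Mini' and 20 'Midi' children, with the same mix in both groups. Suppose exposed 'Midi' children have 2 to 4 tests on record, and non-exposed 'Midi' children have none but stay in the denominator as not abnormal. With s between 0.5 and 1:
- p = 0.05: 12.4% to 18.5% exposed v 0.6 × 9.75% = 5.9% non-exposed, ratio 2.1 to 3.2.
- p = 0.096: 22.8% to 33.2% v 0.6 × 18.3% = 11.0%, ratio 2.1 to 3.0.

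If instead only children with a test on record count, the non-exposed 'Midi' children are those tested for a clinical reason. Their rate cannot be derived from the protocol and could push the comparison the other way.

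**Step 5: after the fix.** Restricted to visits 1 and 2, both groups have two scheduled tests. Under no effect each visit shows p in both groups. The two-visit rates also agree: 9.8% v 9.8% at p = 0.05 and 18.3% v 18.3% at p = 0.096. This assumes equal uptake of the optional tests.

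**The case against.** **A later plan can set the rule.** Sections 13.3 and 15.1 promise a statistical analysis plan before final analysis, and choosing a window and denominator is ordinary work for it. The phrase ever abnormal is also not the protocol's own. That is fair, but the unequal schedule, the pooling of sources and the between-group test are already fixed in the protocol, and together they produce the problem if followed as written.

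**The study is descriptive.** Its objectives are to collate and record, no sample size is set, and no confirmatory claim rests on this test. The list of confounders is open-ended. This stands, and it lowers the severity.

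**Late enrolment is acknowledged.** Section 15.4.2 names first visits at up to 12 months as a limitation and plans a sensitivity analysis at six months. This stands for age at entry; it does not deal with the number of tests.

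**Stronger readings that the documents do not support**
- A reader might take a doubling as the expected size. It is a ceiling: infants exposed only in utero have the same two scheduled tests as non-exposed infants.
- A reader might infer that three-monthly and triggered tests inflate the count further. In 'Mini' only the result nearest each visit is recorded, and triggered repeats follow an abnormal value in a child who already counts.
- A reader might infer that the pooled comparison must be biased upwards. Its direction depends on whether untested 'Midi' children are in the denominator.
- A reader might extend the point to lung clearance index, since Table 3 shows "Lung clearance index^6^ | X | X | X". The number of those tests depends on age at recruitment, and section 6.1 offers exposed and non-exposed children the same investigations. No exposure bias follows.

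**Conclusion.** The point holds for 'Mini'. Under the plain reading of the endpoint, scheduled testing alone raises the rate in the exposed group. The upward direction follows from the protocol for any positive share of exposed infants who reach visits 3 and 4, given comparable follow-up and uptake. The size rests on assumed per-test rates and on that share: a ratio of 1.0 if none do, about 1.4 if half do, and about 1.7 to 2.0 if all do with independent results, falling to about 1.35 with within-child correlation 0.5.

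For the pooled endpoint, the supported conclusion is that the groups are not comparable. The ratios of 2.1 to 3.2 in step 4 apply only if untested children count as normal.

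This should be fixed, but it does not threaten the study, which is hypothesis-generating.

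**What to change.** In sections 15.2.1 and 15.4.2:
- Base the exposed versus non-exposed liver comparison on 'Mini' visits 1 and 2 only. Report it per visit, with the number of children tested as denominator and actual age at sampling shown. Keep late-enrolled infants, with the six-month sensitivity analysis already planned.
- Report visit 3 and 4 results and triggered repeats descriptively for exposed infants, outside the comparison.
- Report 'Midi' record-based results separately, by exposure group, with the number of children who have any test on record.

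**Cost.** Wording only: no new samples, visits or change to testing. The downside is that later tests leave the between-group comparison, so an effect that appears only after six months would be described in exposed infants but not compared. Unequal uptake of the optional tests would remain and would be visible from the numbers tested.
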